# Research protocol: effect of natural S-equol on blood pressure and vascular function- a six-month randomized controlled trial among equol non-producers of postmenopausal women with prehypertension or untreated stage 1 hypertension

**DOI:** 10.1186/s12906-016-1065-5

**Published:** 2016-03-01

**Keywords:** Equol, Supplementation, Blood pressure, Vascular function, Postmenopausal women

## Abstract

**Background:**

Although higher habitual soy intake is associated with lower blood pressure (BP) and stroke incidence, clinical trials using soy protein or isoflavones on cardiovascular risks yielded inconsistent results. The discrepancies are hypothesized to be due to the individuals’ intestinal bacterial capacity to metabolite isoflavones daidzein into equol. Animal and in vitro studies have revealed that equol has stronger estrogen-like and anti-oxidative activity than isoflavones and possesses natriuretic and vasorelaxant properties which may play an important role in the prevention of hypertension. However, no clinical trial has examined the effect of equol on BP. We thus propose a 24-week randomized controlled trial to test the effectiveness of natural S-equol on BP and vascular function among equol non-producers.

**Methods/design:**

This will be a 6-month double-blind, randomized, placebo-controlled trial among 207 non-equol producing postmenopausal women with prehypertension or early untreated hypertension. Eligible participants who have completed a 2-week run-in will be randomized to either one of the 3 groups: placebo group, low-equol group (10 mg/d) and high equol group (20 mg/d). The outcome measures will be conducted at baseline and at the end of the trial including 24 h ambulatory BP, endothelial function (by ultrasound determined brachial flow mediated dilation), arterial stiffness (by pulse wave analysis) and other cardiovascular risk factors (lipid profile, glycemic control and inflammatory biomarkers). Urinary isoflavones will be tested for compliance assessment. One way analysis of variance will be applied to compare the 6-month changes in ambulatory BP or parameters of vascular function among the 3 treatment groups.

**Discussion:**

This study will be performed in community subjects. If the antihypertensive effect of equol is proven, the provision of natural equol to those high risk adults who are unable to produce equol will have enormous public health implications for the primary and secondary prevention of hypertension and cardiovascular diseases on a population basis. The research efforts will also have significant implications for industry in the provision of suitable soy products for the prevention of hypertension and its related complications.

**Trial registration:**

The trial was registered in ClinicalTrials.gov with identifier of NCT02515682.

## Background

### Hypertension is an important public-health challenge

Hypertension is an independent risk factor for cardiovascular diseases (CVD) and renal impairment [1]. An estimated 1 billion individuals are hypertensive worldwide which is estimated to increase to 1.56 billion by 2025 [2]. The risk of CVD will double with each increment of 20/10 mm Hg (SBP/DBP) from 115/75 mm Hg onwards [3]. A meta-analysis by He et al. [4] reported that 49.5 % of strokes in a Chinese population could have been prevented if hypertension was eliminated. A reduction of systolic BP by only 2 mmHg may result in a 6 % reduction in fatal stroke and a 4 % reduction in coronary heart disease (CHD) [5]. Thus, the prevention among the early stage of hypertension will have enormous public health implications.

Prehypertension (SBP 120–139 mm Hg or DBP 80–89 mm/Hg) was the strongest predictor of incident hypertension and associated with elevated risk of incident CVD [3, 6]. Vason et al. [7] observed a 30 % conversion of prehypertension to hypertension over 4 years in the Framingham cohort study. The conversion is even higher in women than men and incident hypertension is highest in women aged above 55 y [8]. Hong Kong 2003/2004 Population Health Survey [9] reported that prehypertension has the highest prevalence of 42 % in midlife women aged 50–59y. Pre-hypertension and its progression to hypertension and increased risk of CVDs have enormous public health implications but the treatment of prehypertension is still debatable [10]. Life-style modification for prehypertension is recommended [3, 11] but compliance is generally poor. Treatment by antihypertensive drugs often produces more or less drug related adverse events, thus the use of natural remedies has aroused increasing interests.

### Vascular function assessment by endothelial function and arterial stiffness

Hypertension is associated with exaggerated functional vascular damage such as endothelial dysfunction and increased arterial stiffness [12]. Endothelial dysfunction is characterized by a reduced capacity of endothelial cells to suppress processes of inflammation, thrombosis and oxidative stress. Impaired arterial elasticity causes increased cardiac after-load, coronary arterial blood supply, atherogenesis and microvascular damage [13]. Vascular dysfunction is considered as a central pathophysiologic process in the initiation and progression of hypertension and atherosclerosis. Evidence shows lifestyle modification can help restore endothelial function (EF) and arterial elasticity. Vascular function can be detected early by several non-invasive methods such as high-resolution ultrasound and tonometry system. Brachial flow mediated dilation (FMD) and pulse wave analysis (PWA) are valuable surrogate markers of vascular function in hypertensive and other cardiovascular conditions [14].

### Soy, equol and hypertension or cardiovascular health

Soy is a traditional Asian diet. Several large scale cohort studies [15, 16] have revealed that the higher habitual soy foods or isoflavones intake is associated with lower BP and cardiovascular incidence. However, the effective components of soy and the underlying mechanisms are still unclear. Soy protein and isoflavones are the most studied components in soy with regard to potential health benefits. However, clinical trials using soy protein and/or isoflavones have yielded mixed findings on cardiovascular risks [17, 18]. The discrepancies are hypothesized to be associated with the individuals’ intestinal capacity to metabolite isoflavones daidzein (one principle isoflavone) into equol [18]. Setchell et al.[19] proposed that equol could be the key molecule accounting for the health benefits of soy or isoflavones. Equol is a metabolite of isoflaovone daizein by intestinal bacteria. Though the majority of animals produce equol, only 20-50 % human adults produce equol following soy/daidzein challenge.

Observational studies have suggested that equol production was associated with decreased risk of certain diseases or conditions such as breast cancer [20], obesity [21], menopausal symptoms [22], hypertension and vascular dysfunction [23, 24]. Our recent published data [25] among 648 prehypertensive postmenopausal women also indicated that equol producers had lower systolic BP (134.8 ± 19.3 vs 138.6 ± 24.8 mmHg, *p* = 0.028), serum triglyceride (1.29 ± 0.63 vs 1.40 ± 0.78 mmol/l, *p* = 0.023), total cholesterol (5.61 ± 0.94 vs 5.77 ± 0.90 mmol/l, *p* = 0.046) and free fatty acid (550.3 ± 200.5 vs 616.6 ± 206.1 μmol/l, *p* = 0.005) than equol non-producers.

Clinical trials have reported that the beneficial effect of soy on cardiovascular health was only present or more pronounced in equol producers than non-producers on the improvement of lipids profiles [26–28], blood pressure [28, 29], vascular function [29, 30] and inflammatory markers [30], although some did not [31, 32]. However, most of these findings are from non-prespecified subgroup analysis of equol-producers, not randomized accordingly.

Equol is currently attracting considerable interest as a potential pharmaceutical or nutraceutical agent [33]. Equol occurs as two enantiomeric forms, S-equol and R-equol, and presents in vivo only as the S-equol [19]. S-equol has a much higher apparent bioavailability (near half of it circulates in the free form) [33] and slower clearance rate (the terminal elimination half-life of 7–8 h) than its precursor daidzein [33]. Equol is superior to all other isoflavones in its estrogenic property and antioxidant activity [34, 35]. In vitro cell culture and animal studies [36–39] have demonstrated that equol possesses natriuretic and vasorelaxant properties via increasing the transcription of endothelial nitric oxide synthase (eNOS) and redox-sensitive genes, enhancing renal blood flow and sodium excretion, which plays an important role in the attenuation of the development of hypertension. To date, several clinical trials have reported favorable effects of S-equol on reducing bone resorption [40], alleviating menopausal symptoms [41, 42], improving glycemic control and reducing LDL-c [43]. However, no randomized controlled trial (RCT) has tested the effect of natural S-equol on BP and vascular function among prehypertensive population.

### Knowledge gap on equol and hypertension or vascular function

Although dozens of studies have examined the effect of soy on BP and cardiovascular health, clinical trials directly using natural S-equol as supplement are limited. Most of these studies have relatively short duration and the criteria for determining equol producing status are not consistent across all the studies. To date, no RCT has tested the effect of S-equol on 24 h ambulatory BP and vascular function among pre-hypertensive subjects. Among previous studies on the soy and cardiovascular health, BP was always taken in one or two clinic occasions with few data on ambulatory BP measurement. It has been well established that ambulatory BP (ABP) monitoring offers substantial advantages over conventional clinic measures due to a good reproducibility and precision, reducing placebo effect and excluding white-coat influence.

### The study hypotheses and purpose

To address the above limitations, we propose to perform a 24-week randomized controlled trial (RCT) among non-equol producing post-menopausal women with pre-hypertension or initial untreated hypertension to verify if natural S-equol has anti-hypertensive effects or can improve vascular function and other cardiovascular risks (lipids, glucose, and inflammatory biomarkers). To control for the influence of equol phenotype, we will limit the participants to non-equol producers since self-produced equol from habitual soy intake in equol producers may neutralize the health effect of equol supplementation. Considering a high prevalence of prehypertension in midlife Hong Kong women [9] and a relatively good compliance of intervention in this age group in our previous trial [44], the study will be conducted in postmenopausal women. We hypothesized that natural S-equol could decrease BP and improve vascular function in equol non-producers of postmenopausal women with untreated prehypertension or early hypertension. There is a dose–response effect with higher dosage of natural S-equol producing more prominent effects on these health outcomes than that of low dose.

## Method/design

This study will be a 6-month double-blind, randomized, placebo-controlled trial with three intervention arms.

### Participants

Our recently completed RCT [45] has screened out 292 equol non-producers of postmenopausal women with untreated prehypertension or hypertension. Subjects have been recruited from community or health assessment center via advertisements in newspaper or referrals. They were initially screened using a standardized questionnaire and their eligibility will be further confirmed at research centre based on the pre-defined criteria.

### Inclusion criteria

Hong Kong Chinese women aged 45–65 y with 2 ~ 8 years menopausal; mean SBP above 130 mmHg or DBP above 80 mmHg or both based on an average of 6 BP readings on two different occasions measured by sphygmomanometer. Equol non-producer is defined as 24-hour urinary log_10_*S-equol*:daidzein ratio less than −1.75 after daidzein challenge (60 mg daidzein daily for 7 consecutive days) [46]. Written informed consent will be obtained from all the participants prior to enrolment. Ethics approval has been obtained from the Clinical Research Ethics Committee of the Chinese University of Hong Kong (CREC Ref. No.: CRE-2013.119-T).

### Exclusion criteria

Subjects on anti-hypertensive medication or with average SBP ≥ 160 or DBP ≥ 100 or both; use of medications known to affect BP within past 6 months (hormone therapy, hypoglycemic or weight reduction agents); medical history or presence of certain chronic diseases (stroke, cardiac infarction, severe liver and renal disease etc.) that could affect BP or limit the individual’s ability to participate in the study; present or history of breast cancer, endometrial cancer, ovarian cancer, thyroid disorder, abnormal uterine bleeding after menopause; on diet for weight loss, glucose or cholesterol reduction or vegetarian diet; regular smoker or alcohol consumption more than 30 g/day; known soy allergy.

### Sample size planning

Our previous RCT [47] on soy showed a 4.2 mmHg net reduction (SD of change 10 mmHg) in SBP after 6-month soy protein and isoflavones supplementation relative to placebo group among 130 pre- and hypertensive postmenopausal women [48]. Assuming a reduction of 5 mmHg of treatment effect on SBP (main effect), 63 subjects per group will yield a power of at least 80 % at 5 % level of significance (for a 2-side t-test). Allowing for 10 % non-compliance or drop out from the study, 69 subjects per group and a total 207 subjects (63 × 3 × 110 %) will be recruited. Similar attrition rates (7.8 % and 7.0 %) have been reported in our previous soy trials [45, 49].

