### Statistical analysis

Relevant parametric and non-parametric tests will be used for testing the differences in the baseline characteristics and outcomes of post treatment among the three study groups. The major approach of analysis will be one way analysis of variance (ANOVA) to compare the change and percentage change of outcomes at 24 weeks among the three groups. Analysis of covariance will also be made to examine if the results are similar after adjusting for potential confounders. The primary analysis will be an intention to treat (ITT) analysis that included all subjects who are randomized. A secondary per protocol analysis will be performed including subjects with good compliance (defined as subjects who consumed ≥ 80 % of provided supplements or with urinary isoflavones level above predefined values for valid users). The non-compliant subjects will be described and compared to the compliant subjects. Dose-dependent effects will be evaluated with the Jonckheere’s trend test. The Bonferroni test will be used for post hoc multiple comparisons among the three groups. The primary outcome variables of 24 h ambulatory BP (mean SBP and mean DBP in all day) will be tested at a significance level of 2.5 % in order to maintain an overall 5 % level. The two important secondary outcomes for assessment of vascular function (%FMD and PWV) will be tested at a significant level of 1.25 %. Exploratory analyses will be used to test each of the tertiary outcomes at the 5 % significance level. Further stratification analysis will be conducted to examine if the effects differed across subgroups such as years since menopause and BMI etc.

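### The stated 80% power is for a two-group t-test at 5%, but each primary blood pressure variable is tested at 2.5% by a three-group ANOVA, whose power is about 60% to 75%

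*Protocol article*

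**What the plan says.** Protocol article, Sample size planning: the inputs are an earlier soy trial's "4.2 mmHg net reduction (SD of change 10 mmHg) in SBP" and a planning effect introduced as "Assuming a reduction of 5 mmHg of treatment effect on SBP (main effect"). The conclusion is that "63 subjects per group will yield a power of at least 80 % at 5 % level of significance", for a two-sided t-test. For 10% loss the number is raised: "69 subjects per group and a total 207 subjects (63 × 3 × 110 %) will be recruited". The section names one variable, systolic pressure, and one two-group test.

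Protocol article, Statistical analysis: the main method is a one-way ANOVA of the 24-week changes across the three arms. There are two primary variables, mean 24 h systolic and mean 24 h diastolic pressure, and they "will be tested at a significance level of 2.5 % in order to maintain an overall 5 % level". On pairs of arms it adds: "The Bonferroni test will be used for post hoc multiple comparisons among the three groups". It gives no significance level for that post hoc step.

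**The concern.** The two sections use different significance levels and different tests for the same primary variable. Systolic pressure, on which the trial is sized, is never tested at 5% in the analysis section, and the lead test there is not a two-group test. An unseen analysis plan would not resolve this, because the article states both levels and they disagree.

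Power is the protocol's justification for 207 women. A reader who takes the 80% at face value will expect a true 5 mmHg effect to be missed in 20% of such trials. If the real figure is higher, a null result will be read as stronger evidence against equol than the design can give. The gap is widest for a graded response, which is the pattern that the article's hypothesis section puts forward.

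**Working it through.** **Inputs.** Difference δ = 5 mmHg, SD of change σ = 10 mmHg, n = 63 per group, two-sided 5% (Sample size planning). Level 2.5% for each primary variable, three-group ANOVA, Bonferroni post hoc (Statistical analysis). The SD of 10 is quoted from the earlier trial and not restated as the planning value, but it is the value that reproduces 63.

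**1. The plan's own figure.** n = 2(z₀.₉₇₅ + z₀.₈₀)²σ²/δ² = 2 × (1.960 + 0.842)² × 100/25 = 62.8, so 63 per group. The noncentrality is δ/(σ√(2/n)) = 5/(10 × √(2/63)) = 2.806. Power is Φ(2.806 − 1.960) = 80.1% by the normal approximation and 79.5% by the noncentral t with 124 degrees of freedom. The stated figure is reproduced, but only at 5%.

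**2. One two-group comparison at 2.5%.** The noncentrality is unchanged and the critical t rises from 1.979 to 2.269. Power is 70.4% (71.4% by the normal approximation).

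**3. The planned ANOVA at 2.5%.** Noncentrality λ = nΣ(μᵢ − μ̄)²/σ², with 2 and 186 degrees of freedom and critical F 3.763.

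| Arm effects, mmHg (placebo/low/high) | λ | Power at 2.5% |
|---|---|---|
| 0/5/5 or 0/0/5 | 63 × 16.67/100 = 10.5 | 74.7% |
| 0/2.5/5 | 63 × 12.5/100 = 7.875 | 59.8% |

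**4. One named pair after Bonferroni.** The level for this step is not stated, so each row is an assumption.

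| Reading | Level per pair | Power (t) |
|---|---|---|
| Three pairs within 2.5% | 0.83% | 55.1% |
| Two comparisons with placebo within 2.5% | 1.25% | 60.8% |
| Three pairs within 5% | 1.67% | 64.8% |

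Under the first reading, the chance of finding at least one active-placebo difference is about 72% by simulation if both doses give 5 mmHg.

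**5. Sensitivity to the SD** (63 per group, 5 mmHg, 2.5%).

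| SD, mmHg | Two-group t | ANOVA 0/5/5 | ANOVA 0/2.5/5 |
|---|---|---|---|
| 9 | 80.1% | 84.4% | 70.8% |
| 10 | 70.4% | 74.7% | 59.8% |
| 11 | 61.2% | 64.9% | 50.2% |

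**6. If all 69 per group give data** (SD 10, 2.5%): t-test 74.8%; ANOVA 79.2% for 0/5/5 and 64.7% for 0/2.5/5.

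**7. What 80% would take** (two-group t, SD 10). At 63 per group the detectable difference is about 5.5 mmHg at 2.5% and 6.3 mmHg at 0.83%. To detect 5 mmHg, the evaluable number per group is 78 at 2.5% or 99 at 0.83%.

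**Side note on dropout.** 63 × 1.10 = 69.3, taken as 69, and 69 × 0.90 = 62.1. With 62 per group the t-test at 2.5% has 69.6% power, less than one point below 70.4%.

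**The case against.** The sample size paragraph is correct for its own inputs. This is a mismatch between two sections, not a slip of arithmetic. Nor can one say that the size was never recomputed, because the article condenses a fuller protocol that is not shown. Both points stand.

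A reader might infer that the design simply has 70% or 55% power. The documents do not support that. The 70% is for a two-group test at 2.5%, whereas the lead analysis is the ANOVA, whose power depends on an arm pattern that the sample size section does not state. In the favourable pattern it is about five points short of 80%. The 55% needs two further steps: that Bonferroni splits the 2.5% over all three pairs, and that one named pair decides the trial. The article says neither.

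A reader might also count the dropout inflation as a second fault. It carries almost no weight. The same paragraph cites attrition of 7.8% and 7.0% in earlier trials, which would leave 69 × 0.922 = 63.6 or 69 × 0.930 = 64.2 per group.

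Finally, the SD comes from a soy protein and isoflavone trial, and the article does not say whether that was clinic or ambulatory pressure. Elsewhere it credits ambulatory monitoring with better precision. At SD 9 the two-group test at 2.5% just reaches 80% and the ANOVA passes it for 0/5/5. This is a reason to show a range, but it does not rescue the stated figure, which was derived with SD 10.

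**Conclusion.** The point holds in this form: the stated power is not a property of the planned primary test. With 5 mmHg, SD 10 and 63 per group, power for systolic pressure at 2.5% is about 75% for the ANOVA under 0/5/5 or 0/0/5 and about 60% under 0/2.5/5. A true effect would be missed in about 25% to 40% of trials, against the 20% implied. At this SD none of the readings above reaches 80% with 63 per group, and full data on all 69 brings the ANOVA to 79.2% at best.

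The ANOVA figures rest on the SD of 10 and on the assumed arm pattern. The pairwise Bonferroni figures, 55% to 65%, also rest on a level that the article does not give. Everything here concerns systolic pressure, because the article states no effect or SD for diastolic pressure.

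**What to change.** Keep 207 women and reword the sample size paragraph in one of two ways.

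- Give the power at 2.5% for the planned ANOVA and name the arm pattern: about 75% for 0/5/5 or 0/0/5 and about 60% for 0/2.5/5, with SD 10 and 63 per group.
- Or give the pairwise difference detectable with 80% power: about 5.5 mmHg at 2.5%, or about 6.3 mmHg at 0.83% if that pairwise level is intended.

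In either case, show the dependence on the SD over a range such as 9 to 11 mmHg, and state the level at which the Bonferroni comparisons are made. If the dropout sentence is being edited anyway, 63/0.9 = 70 is the number that keeps 63 after 10% loss, but that change is optional.

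The cost is a less favourable power statement. No patients, visits or measurements are added, and the analysis stays as planned.

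### One 10 % headcount inflation is made to cover non-compliance as well as drop-out, but the primary ITT analysis keeps non-compliers, so the stated 80 % power is not assured

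*Protocol article*

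**What the plan says.** Under Sample size planning, the protocol article starts from an earlier soy trial with a "4.2 mmHg net reduction (SD of change 10 mmHg) in SBP". It then sets the effect for this trial: "Assuming a reduction of 5 mmHg of treatment effect on SBP (main effect"). The result is "63 subjects per group will yield a power of at least 80" %, "at 5 % level of significance (for a 2-side t-test").

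The allowance follows: "Allowing for 10 % non-compliance or drop out from the study, 69 subjects per group and a total 207 subjects", computed as ("63 × 3 × 110 %) will be recruited". The support offered for the 10 % is attrition: "Similar attrition rates (7.8 % and 7.0 %) have been reported in our previous soy trials". No non-compliance rate is cited.

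Under Statistical analysis: "The primary analysis will be an intention to treat (ITT) analysis that included all subjects who are randomized". Compliance enters only through a secondary per-protocol analysis, limited to women who took at least 80 % of the supplements or met a urinary isoflavone criterion.

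**The concern.** Adding women to the recruitment target replaces observations that will be absent from the analysis. That suits drop-out. It does not suit non-compliance when the primary analysis is ITT, because a non-complier still contributes a 24-week blood pressure to her arm. If she has little or none of the treatment effect, she pulls the mean difference down. The sample size section counts her as lost, while the analysis section counts her as present with, possibly, a smaller effect. A headcount inflation that includes non-compliance fits the secondary per-protocol analysis, not the named primary one.

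At stake is the power figure that readers will use to interpret a non-significant ITT result. If the true figure is a few points lower, such a result says slightly less against a 5 mmHg effect than the article implies.

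**Working it through.** **Inputs from the protocol article.** Effect 5 mmHg, SD of change 10 mmHg, two-sided 5 % t-test, 63 per arm before and 69 after inflation, and a 10 % allowance for non-compliance or drop-out (all Sample size planning). Primary analysis by ITT (Statistical analysis).

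**Assumptions, because the article does not give them.** (a) The split of the 10 % between drop-out and non-compliance. (b) The share of the effect that non-compliers keep. (c) Drop-outs contribute no 24-week outcome. (d) The SD stays at 10.

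**Step 1: reproduce the plan's figure.** Normal formula: n = 2 × 10² × (1.960 + 0.842)² / 5² = 62.8, so 63 per arm. Power at 63 is 80.1 % by the normal formula. By noncentral t, which matches the named t-test, the noncentrality is 5 / (10 × √(2/63)) = 2.81 and power is 79.5 % (64 per arm gives 80.1 %). The plan's figure reproduces to within rounding.

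**Step 2: the inflation.** The plan multiplies: 63 × 3 × 1.10 = 207.9, taken as 207, or 69 per arm. Replacing a 10 % loss requires division: 63 / 0.9 = 70 per arm. With 69, a 10 % loss leaves 69 × 0.9 = 62.1. The loss that 69 can absorb is 1 − 63/69 = 8.7 %. The cited attrition of 7.0 % and 7.8 % would leave 64.2 and 63.6 per arm, with power of 80.3 % and 79.9 %.

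**Step 3: power of the ITT comparison when the allowance is used in full.** Let d be the drop-out proportion, c = 0.10 − d the non-compliers, and k the share of the effect that they keep.

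- n per arm = 69 × (1 − d)
- ITT effect = 5 × (0.90 + c × k) / (1 − d)

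Noncentral t, two-sided 5 %, SD 10, one equol arm against placebo:

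| Drop-out | Non-compliance | Effect kept by non-compliers | n per arm | ITT effect (mmHg) | Power |
|---|---|---|---|---|---|
| 10 % | 0 % | not applicable | 62.1 | 5.00 | 78.9 % |
| 7.8 % | 2.2 % | none | 63.6 | 4.88 | 78.0 % |
| 5 % | 5 % | none | 65.6 | 4.74 | 76.8 % |
| 0 % | 10 % | none | 69 | 4.50 | 74.7 % |
| 0 % | 10 % | half | 69 | 4.75 | 79.1 % |
| 0 % | 10 % | three quarters | 69 | 4.875 | 81.1 % |

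**Step 4: what full dilution would require.** With 10 % non-compliers and no effect in them, 80 % power needs 79 per arm by noncentral t (78 by the normal formula, which is 63 / 0.9² = 77.8). A single inflation of about 10 % does not reach that.

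**The case against.** The strongest reply is that the shortfall is small and its size is assumed. The 74.7 % needs three things together: nobody drops out, all 10 % are non-compliers, and none of them gets any benefit. The article points away from that combination. It supports the 10 % with attrition alone. Its per-protocol threshold is 80 % of supplements, so a woman can be non-compliant while taking most of her doses. Its run-in admits only women who took at least 90 % of the packets. All of this stands, and it is why the result is a range. With partial intake, power can exceed 80 %.

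A second reply is that the 5 mmHg may already be an average over all randomised women. The article does not say that it is an effect in full compliers. If it is an ITT average, there is no dilution to correct. But non-compliance then needs no place in the allowance, so the wording still needs attention.

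A reader might infer that the trial cannot reach 80 % power, or that the multiplication by 110 % is what breaks the calculation. Neither is supported. Some scenarios within the allowance give 81 %. The multiplication costs one woman per arm and about half a point of power (79.5 % at 63 against 78.9 % at 62.1), and 69 per arm is enough for the cited attrition by itself.

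A reader might also add the loss from testing the primary outcomes at 2.5 % when the trial was sized at 5 %. That is a separate inconsistency and should be dealt with on its own.

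**Conclusion.** The concern holds in a limited form. The allowance and the primary analysis set do not fit together: non-compliance is budgeted as lost sample, yet non-compliers remain in the ITT comparison. The stated figure of at least 80 % is therefore not assured for the named primary analysis under the plan's own 10 % allowance. It is not shown to be out of reach either.

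Across the scenarios tabulated, power runs from about 75 % to 81 % at the 5 % level. The lower end assumes no effect in any non-complier and the upper end assumes that three quarters of it is kept. If most of the allowance is drop-out, as the cited attrition suggests, power is about 78 % to 79 %. The shortfall is thus between nothing and about 5 points. The inflation formula is a minor supporting correction.

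**What to change.** Keep 207 women and change the wording of Sample size planning in one of two ways.

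1. Reserve the allowance for missing 24-week outcomes, state that 69 per arm covers 8.7 % missing, and define the 5 mmHg as the mean effect over all randomised women, non-compliers included. Drop non-compliance from the allowance.
2. Keep non-compliance in the allowance, but state the assumed split between drop-out and non-compliance and the effect expected in non-compliers. Then restate ITT power as about 75 % to 81 % at the 5 % level, in place of the flat figure.

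Under either option, correct the inflation for missing outcomes to n / (1 − d), which gives 63 / 0.9 = 70 for a 10 % loss, or say that 69 covers 8.7 %.

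The cost is a few sentences and, under the second option, a somewhat less favourable power statement. No extra participants are needed, and neither the design nor the analysis changes.
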